#### Sensitization workshop.

Teachers will play a pivotal role as integral members in the course of implementing group sessions. A separate sensitization workshop will be conducted for teachers who will facilitate the intervention phase on behalf of the school. This workshop is designed to enable teachers to actively facilitate group sessions addressing crucial issues like excessive social media usage, child-family relationships, alcohol consumption, as well as sexual health issues, fostering a collaborative and engaging environment. By actively involving teachers in the execution of these sessions, the campaign becomes ingrained in the school's culture, ensuring its enduring impact.

### Phase 2: The Intervention Phase

#### Sample size for the intervention phase.

For Phase 2, based on the available literature on sample size guidelines for Randomized Controlled Trials. [17], for a 95% confidence level for the two-tailed hypothesis (${\text{Z}}_{\alpha }$= 1.96) and to achieve a power of 90% (${\text{Z}}_{\text{1}-\beta }$ = 1.2816), with an assumed standard deviation of population 0.15 and estimated effect size (D) of 5%, a minimum sample size of 189 per arm/group is required for the study, as per the following for the cluster-level randomization:

$$\begin{array}{c} \text{n}=\frac{{\;\text{2}\left({\text{Z}}_{\alpha }+{\text{Z}}_{\text{1}-\beta }\right)}^{\text{2}}\sigma^{\text{2}}}{(D{)}^{\text{2}}} \end{array}$$

By considering an attrition rate (10%), the sample size for each group (control and intervention) has come out to be approximately 208 participants in each of the control and intervention groups. Therefore, the minimum sample size for both control and intervention groups comes out to be 416 per study location. The total sample size is estimated to be n is equal to 1248, including all three cities in Northern India. To align with the baseline sample size, the RCT will also include 1,260 participants across all three cities.

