#### Sample size for baseline assessment.

For Phase 1 (baseline assessment), the sample size is calculated using the formula n = 4pq/d^2^ [9]. Where n is the sample size for each area of Tricity, p is the prevalence, q is 1-p, and d is precision. The proportion of adolescents in India is approximately 20% [10]. The prevalence of alcohol consumption among adolescents at least once a year ranged from 10.6% to 32.9% [11]. *Prevalence of sexual activity ranged between 16.9%* [12] *to 21%, and sizable numbers of Indian adolescents were facing parent-child conflicts. Therefore,* assuming a prevalence of 20%, a precision of 4%, and an attrition rate of 5%, the target sample size is calculated as 420 for each of the three cities. Taking an equivalent number of samples from each of the three cities, the final sample size for all three study areas is 1260.

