### Statistical analysis

All analyses will be conducted on a modified intention-to-treat (ITT) population, comprising all randomized participants with a completed baseline and at least one completed valid post-baseline assessment.

The study will incorporate the use of generalized estimating equations (GEE) as the regression model to analyze the changes in study outcomes (social media use and its attributable child-family relationship, alcohol consumption, as well as sexual health issues) over the specified periods. The formal mathematical framework and specification of the GEE model equations are provided in S6 File. This comprehensive approach will provide more accurate and reliable insights into the effectiveness of the intervention across different socio-demographic variables, economic variables, and time intervals in the data.

The GEE model shall be adjusted for different socio-demographic and economic variables as well. GEE is applicable for both continuous and categorical study outcomes, and in the present study, the outcomes are both metric and categorical. For categorical outcomes, the GEE procedure can be executed with the maximum likelihood estimation (MLE) algorithm described

Additionally, a repeated measures analysis of ANOVA shall be used to study the effectiveness of the intervention across different periods of intervention. The statistical analysis shall be carried out using Stata version 17. The results will be considered statistically significant if the P-value is less than 0.05.

Further, the qualitative assessment of the exit interviews to elicit feedback and identify general challenges/barriers in executing the intervention will be analysed using thematic analysis and transcript interpretation by employing open-source MAXQDA software.

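### The 90% power claim rests on an SD of 0.15 and a 5% effect tied to no outcome, and it cannot extend to binary outcomes with prevalences near 20%

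*Protocol article*

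**What the plan says.** The section on sample size for the intervention phase (Protocol article) uses the two-means formula "for a 95% confidence level for the two-tailed hypothesis" and "to achieve a power of 90" per cent, "with an assumed standard deviation of population 0.15 and estimated effect size (D) of 5" per cent. It concludes that "a minimum sample size of 189 per arm/group is required for the study". Allowing for 10% attrition, this becomes "approximately 208 participants in each of the control and intervention groups", then 416 per study location and 1,248 over three cities, raised to 1,260 to match the baseline sample. No outcome, scale or source is given for the SD. The text does not say whether 5% is absolute or relative.

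The section on sample size for the baseline assessment, which concerns the same cohort, cites prevalences of 10.6% to 32.9% for alcohol consumption and 16.9% to 21% for sexual activity. It works from one value, "assuming a prevalence of 20%, a precision of 4" per cent.

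The statistical analysis section lists social media use, child-family relationship, alcohol consumption and sexual health issues as outcomes, and states that "in the present study, the outcomes are both metric and categorical".

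**The concern.** The power statement is made for the study as a whole, but it depends on one SD and one effect that belong to nothing named. The only outcome figures in the article are prevalences. For a proportion the SD is not a free assumption, because the prevalence fixes it, and none of the cited prevalences gives a value near 0.15.

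Alcohol use and sexual behaviour are among the trial's stated targets. If they are analysed as proportions, a reader who relies on the published 90% could take a non-significant result as evidence against a 5-point effect, when the trial had far less chance of finding one.

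**Working it through.** **Inputs from the article.** z-values 1.96 and 1.2816; SD 0.15; D 0.05; 189 per arm per city; 10% attrition; 1,260 pupils; 12 schools, 6 against 6, with 105 pupils each; prevalences as cited.

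**Assumptions, not in the article.** D is an absolute fall from 20% to 15%. The ICC is 0.01 or 0.02. Pupils analysed per school are 105 × 0.9 = 94.5, so 6 × 94.5 = 567 per arm, which equals 3 × 189. With no loss it is 630 per arm.

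**1. The plan's own figure.** n = 2 × (1.96 + 1.2816)² × 0.15² / 0.05² = 2 × 10.508 × 0.0225 / 0.0025 = 189.1. Then 189 × 1.10 = 208, × 2 = 416, × 3 = 1,248. The stated figures reproduce.

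**2. SD of a proportion, sqrt(p(1 − p)).**
- 20%: sqrt(0.20 × 0.80) = 0.40
- 10.6%: sqrt(0.106 × 0.894) = 0.31
- 32.9%: sqrt(0.329 × 0.671) = 0.47
- 16.9% and 21%: 0.37 and 0.41

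An SD of 0.15 requires p(1 − p) = 0.0225, so p = 2.3% or 97.7%. From 2.3%, a 5-point fall is impossible.

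**3. Power for 20% against 15%.** The variance sum is 0.20 × 0.80 + 0.15 × 0.85 = 0.2875. Power = Φ(0.05 / sqrt(0.2875 × DEFF / n) − 1.96), where the design effect is DEFF = 1 + (94.5 − 1) × ICC.

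| n per arm | DEFF | z-ratio | Power |
|---|---|---|---|
| 189 (one city) | 1 | 1.282 | 25% |
| 567 (pooled, after loss) | 1 | 2.220 | 60% |
| 630 (pooled, no loss) | 1 | 2.341 | 65% |
| 567, ICC 0.01 | 1.935 | 1.596 | 36% |
| 567, ICC 0.02 | 2.87 | 1.311 | 26% |

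**4. Number needed for 90% power, before clustering and attrition.** 10.508 × 0.2875 / 0.0025 = 1,208 per arm. With SD 0.40 in both arms, as in the plan's own formula, 2 × 10.508 × 0.16 / 0.0025 = 1,345 per arm.

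**5. Fall from 20% detectable at 90% power with 567 per arm.** Solve d = 3.2416 × sqrt((0.16 + (0.20 − d)(0.80 + d)) × DEFF / 567). The alternative, SD 0.40 in both arms, is d = 3.2416 × 0.40 × sqrt(2 × DEFF / 567).

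| | Variance from each arm's own proportion | SD 0.40 in both arms |
|---|---|---|
| Unclustered | 7.1 points | 7.7 points |
| ICC 0.01 | 9.5 points | 10.7 points |
| ICC 0.02 | 11.3 points | 13.0 points |

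The first column uses the same variance model as the power figures in step 3.

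**6. Sensitivity to prevalence.** For a 5-point fall, unclustered, power runs from 43% (starting at 10.6%) to 18% (starting at 32.9%) at 189 per arm, and from 87% to 45% at 567 per arm.

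**The case against.** The strongest reply is that the sample-size section uses a formula for means, speaks of a population standard deviation and never says that it concerns a proportion. Several listed instruments are scales (the social media use scale, the family relationship scales, AUDIT), so 0.15 may be the SD of a rescaled score. The 20% belongs to a different calculation, the precision of the baseline estimate. This stands. A reader might infer that the SD contradicts the 20% prevalence, but that holds only if the SD is meant for a proportion, which the article does not state. For a score that really has SD 0.15 and D 0.05, the pooled sample would still have about 91% power at an assumed ICC of 0.02 with 94.5 pupils per school.

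A reader might also infer that the trial has only 25% power. That figure matches how n was built, city by city, but no city-level test is stated and the article describes one trial of 1,260 pupils. The pooled 60% to 65% belongs beside it.

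Nor does the article name drinking prevalence, or a fall from 20% to 15%, as an endpoint. Its results chain speaks of awareness of alcohol risks, and alcohol is measured with AUDIT. The 5-point reading is therefore an assumption. A relative reading does not help: for 20% against 19%, power at 189 per arm is about 4%.

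At the lowest cited alcohol prevalence the pooled shortfall before clustering is small (87% at 567 per arm; about 90% at 630).

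Finally, these figures describe one unadjusted comparison at one time point. The planned covariate-adjusted GEE over repeated assessments could do somewhat better, by an amount that the article gives no means to compute.

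What the reply does not rescue is the breadth of the claim. If 0.15 belongs to a score, the 90% belongs to that score alone.

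**Conclusion.** The point holds in limited form. The 90% power is stated for the study from an SD and an effect tied to no outcome. It can be right at most for an unnamed metric score. It does not carry over to categorical outcomes with prevalences such as the 20% used at baseline.

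If D is a fall from 20% to 15%, power before clustering is about 25% on the per-city number and about 60% to 65% pooled. At an assumed ICC of 0.02 it is about 26% pooled. These sizes rest on the absolute reading of D, a binary outcome starting at 20%, and a simple two-group comparison; the clustered figure also rests on the assumed ICC.

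The arithmetic of the 189 is not at fault, and a direct contradiction between the two sample-size sections is not shown. The fault is a stated power figure that reaches further than its inputs allow.

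**What to change.** In the intervention-phase sample-size section, name the metric outcome and scale to which SD 0.15 and D 0.05 belong, and restrict the 90% claim to it. For binary outcomes, replace that claim with the difference that 1,260 pupils in 12 schools can detect. Use one variance model throughout, and a design effect with an ICC that is stated and labelled as an assumption. The detectable falls in step 5 of the working can serve as a guide: about 7 points unclustered, rising to about 11 at ICC 0.02.

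The cost is one rewritten paragraph. No extra pupils, schools or visits are needed. The article reports that no results exist yet, so the change can be made before outcome data are seen. The price is a less favourable stated figure for the alcohol and sexual-health proportions.

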#### Sampling strategy for baseline assessment.

In total, 1260 adolescents will be recruited from 12 schools (4 schools per city) across three cities in Northern India (Fig 3). These four schools per city will be divided into two government schools and two private schools for socio-economic representation. Each city will recruit 420 adolescents, 105 students per school. We will randomly select 4 classes from the pool of eligible 9^th^-, 10^th^-, 11^th^, and 12th-grade classes, assuming an average class size ranging between 25 and 35 students.

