#### Sampling strategy for randomized controlled trial.

The same COHORT from the pre-intervention phase (baseline assessment) will be followed. Therefore, the 12 schools will be randomly selected into 6 intervention groups and 6 control groups, as shown in Fig 2.

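### The 90% power comes from the formula for independently randomised individuals although whole schools are randomised, so the design as described does not support the figure

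*Protocol article*

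**What the plan says.** The protocol article, under Sample size for the intervention phase, takes a two-sided 5% level (Z = 1.96), 90% power (Z = 1.2816), a standard deviation of 0.15 and a difference D of 5%. It states that "a minimum sample size of 189 per arm/group is required for the study, as per the following for the cluster-level randomization" and then prints n = 2(Zα + Z1−β)²σ²/D². Ten per cent attrition raises 189 to about 208 per group. Two groups give 416 per study location, and three cities give 1248. The trial enrols 1,260 to match the baseline survey.

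The unit of randomisation is the school. Study area and settings has schools randomised to arms within each city, four schools per city. Under Sampling strategy for baseline assessment, "Each city will recruit 420 adolescents, 105 students per school". Under Sampling strategy for randomized controlled trial, "the 12 schools will be randomly selected into 6 intervention groups and 6 control groups". The Statistical analysis section plans GEE models adjusted for covariates, and names no separate test within each city.

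**The concern.** The label and the formula disagree. The text says the calculation is "as per the following for the cluster-level randomization", yet the expression treats every student as an independent observation. Students in one school share teachers, peers and group sessions, so their outcomes are likely to be correlated. With about 100 students per school, even a small correlation inflates the variance of the arm comparison considerably. Only 12 schools carry the information on between-school variation.

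What is at stake is how the result is read. A null finding set against a stated 90% power looks like a well-powered negative. If true power were nearer 55%, that reading would be wrong. Because the required number is built up city by city, a reader may also take 416 students in one city to be an adequately powered comparison.

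**Working it through.** **Inputs from the protocol article.** Two-sided α = 0.05; power 90%; σ = 0.15; D = 0.05, so D/σ = 0.333; attrition 10%; 105 students per school; 12 schools, 6 per arm. Four schools per city randomised within city implies 2 against 2.

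**Assumed, because the documents do not give it.** The ICC, taken over 0.01 to 0.05. School sizes are taken as equal, with no precision gain from covariates or repeated measures.

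**Step 1: reproduce the plan's figure.** 2 × (1.96 + 1.2816)² × 0.15² / 0.05² = 2 × 10.508 × 9 = 189.1, the stated 189. Then 189 × 1.10 = 207.9 (208), 208 × 2 = 416 and 416 × 3 = 1248. The arithmetic is right, and it shows that the design effect used was 1.

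**Step 2: add clustering.** Completers per school are m = 105 × 0.9 = 94.5. The design effect is DE = 1 + (m − 1) × ICC = 1 + 93.5 × ICC. With k schools per arm, SE = σ√(2·DE/(k·m)). Power follows from D/SE, by the normal approximation or by a noncentral t with degrees of freedom (df) set by the number of schools.

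Example, pooled, ICC 0.02: DE = 1 + 93.5 × 0.02 = 2.87; SE = 0.15 × √(2 × 2.87/567) = 0.0151; D/SE = 3.31. Power is 91% by normal approximation and 83% on 8 df (critical t = 2.306).

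**Step 3: pooled comparison, 6 against 6 schools (567 completers per arm).** The 8 df are 12 schools less 3 cities less 1 for arm; the 10 df are 12 less 2, ignoring city.

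| ICC | DE | Normal | t, 10 df | t, 8 df |
|---|---|---|---|---|
| 0.01 | 1.94 | 98% | 95% | 94% |
| 0.02 | 2.87 | 91% | 85% | 83% |
| 0.03 | 3.80 | 82% | 74% | 71% |
| 0.05 | 5.67 | 65% | 57% | 54% |

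Power reaches exactly 90% at an ICC of 0.021 (normal), 0.015 (t, 10 df) or 0.014 (t, 8 df). On 8 df, the difference detectable with 90% power is 0.056 at ICC 0.02 and 0.079 at ICC 0.05, against the planned 0.05.

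**Step 4: one city, 2 against 2 schools (189 completers per arm).** This is the level at which 189 was derived.

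| ICC | Normal | t, 2 df |
|---|---|---|
| 0 | 90.0% | 43% |
| 0.01 | 64% | 27% |
| 0.02 | 48% | about 20% |
| 0.05 | 27% | 13% |

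The 90% appears only at an ICC of exactly zero with a normal reference.

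**The case against.** The strongest reply is that the trial does not rest on 189 per arm. It enrols 630 per arm over three cities, and the analysis described is of the whole trial. Tripling a per-city number absorbs a good deal of clustering: at ICC 0.01 pooled power is 94% even on 8 df. As the documents state no ICC, nobody can say from them that pooled power is below 90%. This stands. A reader might infer that the design lacks 90% power outright, and the documents do not support that.

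A second reply is that no city-by-city test is announced, so the per-city figures describe a comparison that may never be made. This also stands. The 43% at ICC 0 comes from choosing a test on 2 df, not from any clustering variance. What remains is that the protocol itself derives its requirement per study location, and at that level the stated power holds only without clustering.

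A third reply is that the break-even ICC depends on the model. The 8 df version charges for the city strata but credits no reduction in between-school variance from randomising within city. It also ignores the baseline measurement, the four later assessments and the planned adjustment. If adjustment removed 25% of the variance at both levels, an assumption made only for illustration, the break-even on 8 df would move from 0.014 to 0.022 and power at ICC 0.02 from 83% to 92%. So 0.014 is not a fixed limit to write into the protocol.

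None of this makes the printed formula a cluster calculation. Any pooled power that survives is a by-product of multiplying by three. Nor is this detail that an article leaves to a fuller document: the formula, its inputs, its label and the resulting power are all stated.

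**Conclusion.** The point holds as a fault of derivation. The multiplication is correct, but the formula does not apply to a school-randomised trial and is wrongly described as doing so. The unconditional 90% is therefore unsupported, which is a weaker statement than saying it is false.

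For the pooled comparison, whether 90% is met turns on an ICC somewhere around 0.014 to 0.021, depending on the reference distribution. Within the assumed range of 0.01 to 0.05, power on 8 df runs from 94% down to 54%. For a single city, 90% is lost at any positive ICC. That should not be read as showing that the protocol plans underpowered city tests, because it announces none. These figures rest on equal school sizes, 2 against 2 schools per city, 10% attrition and no gain from adjustment or repeated measures.

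**What to change.** Replace the formula with a cluster-randomised calculation for the comparison pooled over the three cities: 6 schools per arm, about 95 students analysed per school, a stated and justified ICC, and a small-sample t reference. In place of the unconditional 90%, report power or detectable difference over a range of ICCs. Name the degrees of freedom and any gain assumed from baseline adjustment or repeated measures. A table like that in step 3 would serve, with the authors' own ICC marked. Remove the implication that 416 per location is a powered comparison.

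The cost is a rewritten sample-size paragraph and a less favourable stated power. No extra schools or students are needed. Recruitment is planned to run tentatively to 31/12/2026 and the article reports that no results exist yet, so the change can be made before any are known.

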#### Sampling strategy for randomized controlled trial.

The same COHORT from the pre-intervention phase (baseline assessment) will be followed. Therefore, the 12 schools will be randomly selected into 6 intervention groups and 6 control groups, as shown in Fig 2.

#### Open-label randomized control controlled trial.

Both the study participants and the researchers know which treatment is assigned to them. For the present study, blinding of the investigator and participants is not possible at the time of delivering the intervention, since the study aims to deliver a behaviour-centered intervention executed through a social marketing technique. Further, the investigator is required to build rapport with participants in the intervention group to deliver the intervention and motivate them to continue at each step. The participants shall also be aware that they will be given the intervention; therefore, the trial is open-label in nature. However, data shall be entered and analysed by a blinded/masked researcher.

#### Delivering the intervention.

A novel Social Marketing Intervention (SMI) will be provided for three months, once per month. The duration of each session will be between 1 hour and 1.5 hours. Social marketing is the application of marketing techniques and strategies to the analysis, planning, execution, and evaluation of programs designed to influence the voluntary behaviour of target audiences to improve their health outcomes, personal welfare, and that of their society [18]. The control group shall receive basic counselling consisting of awareness aimed at limiting social media use. An early version of the intervention is attached in the S5 File.

### Phase 3: Post-intervention phase

Assessments of outcomes will be conducted after completing the three-month intervention phase and for three months following the intervention closure. The Social Media Use Scale (SMUS), Family Relationship Scales, Family Leisure Activity Profile, WHO’s Alcohol Use Disorders Identification Test (AUDIT), and Sexual Health Practice Tool tools will be administered at baseline (T0) and at four time points after implementation of the intervention. The time points will include immediately post-intervention (T1) and at one-month post-intervention (T2), two months post-intervention (T3), and three months post-intervention (T4) for both the intervention and control groups. After three months of active intervention, the follow-up period will be passive. During the three-month follow-up, the intervention maintenance phase will be implemented. Additionally, the utilization of the Readiness to Behaviour Change Questionnaire is planned to assess the stage of behavioural change of students.

Exit interviews (approximately 50 interviews) will be conducted to elicit feedback and identify general challenges/barriers in executing the intervention from parents, teachers, and students as part of the research process

